### Statistical Methods

The demographic and clinical characteristics collected at randomization will be presented as means with SDs or medians with interquartile ranges for continuous variables and as percentages for categorical variables, as appropriate.

For all the outcomes, we will estimate differences in effect size between the groups on both the intention-to-treat (ITT) and per protocol (PP) basis (39). Categorical variables will be compared with the chi-square or Fisher's exact tests and continuous variables will be compared with the Student's *t*-test or the Wilcoxon signed-rank test, as appropriate. The time effect of day the time-to-event outcomes identified (e.g., rate of ready for ECMO weaning, rate of ECMO weaning, rate of mechanical ventilation weaning, all-cause mortality, and rate of major post-ECMO complications) between the groups will be estimated with the Cox proportional hazards regression analysis and graphically illustrated using the Kaplan–Meier methods until CaRe-ECMO days 7, 14, 30, and 90, respectively (40). Variables, including total length of ready for ECMO weaning, total length of ECMO weaning, total length of mechanical ventilation, ECMO unit LOS, and total hospital LOS, will be treated with time-to-event data and will be analyzed with mixed-effects ordered logistic regression (41). Secondary outcomes with normal and non-normal distributions, including CPC, ADL, HRQoL, and diaphragmatic thickness and mobility, will be estimated for group differences with mixed-effects linear regression (41).

Considering that part of patients will definitely not reach the primary endpoint, i.e., ready for ECMO weaning at CaRe-ECMO day 7 for sensitivity purpose, we will assess the heterogeneity of the treatment effect on primary outcome and secondary outcomes in pre-specified subgroups of interest as per baseline data to be collected at randomization (e.g., age, gender, main diagnosis, comorbidities, the APACHE II score, ECMO mode, length since mechanical ventilation) by using exploratory *post-hoc* sensitivity adjusted analyses for any corresponding statistical methods mentioned above.

Interim analysis will be scheduled halfway through enrollment to check that there are no serious issues with respect to sample handling or data collection.

All the analyses will be conducted at a two-sided alpha level of 5% and will be performed using the Stata version 16 (StataCorp, College Station, Texas, USA) or other software, as appropriate.

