### Enrollment, Randomization, and Allocation

Eligible patients who meet the eligibility criteria and are provided with ECMO therapy in our Department of Emergency Medicine will be enrolled in the CaRe-ECMO trial. Their guardians will receive a detailed explanation of trial purpose and procedures. The patients will have a same chance to be randomly assigned to the CaRe-ECMO group or the control group. They also will be informed that they have the right to withdraw from the trial at any time of the trial period.

Simple randomization (1:1) will be applied using a computer generated random sequence, which will be independently administered and concealed by the Clinical Research Board from the School of Public Health of Nanjing Medical University (from here on called allocation center). Once a patient has been deemed eligible and the informed consent form has been signed, an independent trial assistant will register the participant, record her/his group allocation, and reveal the group allocation to those delivering the interventions (21). Figure 1 demonstrates the overview of the recruitment, randomization, and allocation based on the CONSORT principle.

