#### Secondary Outcomes

Secondary outcomes are listed and elaborated as follows:

1) Rate of ECMO weaning will be calculated according to date of ECMO weaning fulfilled.2) Total length of ready for ECMO weaning refers to exact length in day till patients fulfill all the criteria of ready for ECMO weaning according to daily checkout records (14).3) Total length of ECMO weaning refers to exact length in day for patients treated with ECMO therapy (29).4) Rate of mechanical ventilation weaning will be calculated according to date of mechanical ventilation weaning fulfilled. Daily screening of mechanical ventilation weaning will be strictly performed with checklist shown in Table 7 according to the American Thoracic Society and the American College of Chest Physicians Clinical Practice Guideline (30).5) Total length of mechanical ventilation refers to exact length in day for patients treated with mechanical ventilation.6) All-cause mortality is defined as rate of death due to any causes and will be calculated according to date of death (31).7) Rate of major post-ECMO complications refers to rate of complications occurred after ECMO including but not limited to ECMO-related complications (e.g., thromboembolism), mechanical ventilation-related complications (e.g., pneumonia), newly developed myocardial infarction, acute kidney injury, neurologic events (e.g., stroke, seizures), and multiple organ failure (32). Information of major post-ECMO complications will be collected in the Complication Recording Sheet (Table 8).8) Diaphragmatic thickness and mobility refer to ultrasound-guided evaluation of diaphragmatic thickness and mobility under M-mode (33).9) Extracorporeal membrane oxygenation unit LOS accounts for length in day for stay of patients in the ICU unit.10) Total hospital LOS accounts for total hospital LOS in day for stay of patients in both the ECMO unit and other departments.11) Total cost for hospitalization will be calculated by addition of the cost of all the units and department admission.12) Cerebral performance category will be recorded, for those successfully weaning of ECMO, to reflect post-ECMO neurological status (34).13) Activities of daily living will be evaluated, for those successfully weaning of ECMO, with Katz Index (35).14) Health-related quality of life will be measured, for those successfully weaning of ECMO, with SF-12 (36).

**Table 7 T7:** Mechanical ventilation weaning checklist.

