### Sample Size Calculation

We considered the rate of ready for ECMO weaning being conservatively 50% higher in the CaRe-ECMO group than in the control group at CaRe-ECMO day 7 as a clinically meaningful effect, implying a hazard ratio (HR) of 0.5. Accordingly, we performed sample size calculation for the Cox proportional hazards model with an alpha error of 5% and a power of 80%, effect size of HR = 0.5, and overall event (ready for weaning) probability of 30% at CaRe-ECMO day 7 (increases from 30 to 45%) according to our retrospective data analysis and literature review (38). The needed sample size was estimated as *n* = 348, i.e., 174 per group. Due to the relative short observational period and the real-world situation (e.g., patients treated with ECMO therapy generally will not discharge till stable or death), accounting for 5% attrition according to their failing for fulfill of daily eligibility screening for cardiopulmonary rehabilitation during the therapeutic period, the target sample size is set at 366 (183 per group).

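### Two methods named for secondary outcomes do not fit the design: a paired rank test for independent arms, and an ordered logistic model without censoring for durations called time-to-event

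*Protocol article*

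**What the plan says.** Patients are allocated to two parallel arms: "Simple randomization (1:1) will be applied using a computer generated random sequence" (Enrollment, Randomization, and Allocation). No matching or pairing appears anywhere in the article.

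Statistical Methods sets the comparison as one between arms: "For all the outcomes, we will estimate differences in effect size between the groups". It then names methods in layers:

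- **Continuous variables in general:** Student's t-test or "the Wilcoxon signed-rank test, as appropriate".
- **Rates** of readiness, ECMO weaning, ventilator weaning, death and complications: Cox regression and Kaplan–Meier curves to days 7, 14, 30 and 90, besides chi-square or Fisher tests.
- **Five durations** (readiness, ECMO, ventilation, ECMO unit stay, hospital stay): these "will be treated with time-to-event data and will be analyzed with mixed-effects ordered logistic regression".
- **CPC, ADL, HRQoL and diaphragm measures:** mixed-effects linear regression, introduced by "Secondary outcomes with normal and non-normal distributions, including CPC, ADL, HRQoL".

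Under Secondary Outcomes, the first duration is the "exact length in day till patients fulfill all the criteria of ready for ECMO weaning". Statistical Methods also accepts that "part of patients will definitely not reach the primary endpoint" by day 7.

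**The concern.** Both problems are methods that the article names. They are not details left to an analysis plan.

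The signed-rank test works on within-pair differences, and two independent arms have none. Someone following the text literally must either invent pairs or depart from the plan.

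The duration sentence conflicts with itself. Time-to-event data need a method that handles patients whose event is not observed, and an ordered logistic model has no such term. A random effect needs repeated values or clusters. Each patient has one value per duration, no cluster is named, and Trial Setting places the trial mainly in one department. A patient who dies before readiness, or never becomes ready, has no value under the stated definition. A patient who dies in the unit has a stay cut short by death, and the text does not say how that stay is counted.

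At stake is the reading of the secondary outcomes. The Discussion points future trials to them if the primary result is not significant, and its closing paragraph ties the trial's effect on standard care to superiority on primary and secondary outcomes together.

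**Working it through.** The plan gives no figure to reproduce here, so each named method is set against the design, with supporting numbers.

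**1. Signed-rank test**

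*Chance of equal arms.* Inputs: N = 366 (Sample Size Calculation), simple 1:1 randomisation. P(183/183) = C(366,183) / 2^366 = 0.042. In about 96% of realisations the patients cannot all be matched one-to-one. Equal arms would not create pairs either, so this only illustrates the point.

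*What forced pairing does.* Assumed data: lognormal durations (log-mean 2, log-SD 0.8), 183 per arm.

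- One dataset, second arm multiplied by 0.83, re-paired at random 2,000 times: signed-rank p ran from 0.05 to 0.98 (middle 95%: 0.14 to 0.63). The rank-sum test gives one value, p = 0.14.
- No difference, 4,000 simulated trials: rejection rate 4.7% (signed-rank) and 4.3% (rank-sum).
- Second arm multiplied by 0.8, 4,000 trials: power 69% (signed-rank) and 73% (rank-sum).

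So the defect is an arbitrary result and a little lost power. Type I error is not inflated.

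*Reach.* Of the listed secondary outcomes, only total cost has no model of its own and rests solely on the t-test/Wilcoxon sentence. Any other general comparison of a skewed continuous variable is also affected.

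**2. Durations**

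| Feature | Stated or implied in the article | Ordered logistic model as named |
|---|---|---|
| Type of data | time-to-event | no censoring term |
| Values per patient | one per duration | random effect has nothing to act on |
| Clusters | none named; mainly one department | same |
| Death or no event | mortality 40–70% quoted in the Introduction | no rule given |

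*Possible effect on length of stay.* None of the stay or mortality inputs below comes from the article. Assume 183 per arm, the same stay distribution in both arms given survival or death, and deaths entered at their observed length. Stay is 3 + exponential days for deaths and 7 + exponential days for survivors. A rank-sum test at two-sided 5% stands in for the planned model. The last column is the share of trials with a significantly shorter stay in the higher-mortality arm.

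| Mortality | Median of exponential part: deaths / survivors (days) | Share of trials |
|---|---|---|
| 50% vs 40% | 8 / 25 (overall medians 3+8 = 11 and 7+25 = 32) | about 18% |
| 50% vs 40% | 15 / 25 | about 9–10% |
| 50% vs 45% | 8 / 25 | about 7–8% |
| 50% vs 40% | 20 / 20 | about 3–4% |
| 50% vs 50% (check) | 8 / 25 | about 2.5% |

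The last row is the chance level in that direction. The distortion ranges from almost nothing to about seven times chance (18 / 2.5), depending on how much shorter the stays of those who die are and how far mortality differs.

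**The case against.** The strongest reply is that little depends on these sentences.

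- **The primary outcome is safe.** Day-7 readiness has chi-square or Fisher and Cox. This stands.
- **The Wilcoxon name is probably a slip for rank-sum.** That is likely. The qualifier about appropriateness does not cure it, because no unpaired rank test is named.
- **Three of the five durations repeat events already analysed by Cox and Kaplan–Meier.** This stands for censoring. Those analyses still state no treatment of death as a competing event, and the second, ordinal analysis of the same durations remains unexplained.
- **An ordinal model for stay can be sound.** It can, if death is ranked worst. The article gives no ranking, and without one the model does not match data it calls time-to-event.
- **Mortality is analysed separately, so an imbalance would be visible.** It would, but that does not correct the duration comparison.

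Four stronger readings are tempting, and the documents do not support them.

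- A reader might infer that the plan scores early death as a good outcome. The text is silent on this, so the bias is conditional.
- A reader might take "overall event (ready for weaning) probability of 30% at CaRe-ECMO day 7 (increases from 30 to 45"%) to mean that about 229 (183 × 0.70 + 183 × 0.55) to 256 (366 × 0.70) patients are censored in the duration analyses. Those are patients not yet ready at day 7; follow-up runs to day 90 and some become ready later.
- A reader might call the signed-rank p-value invalid. Under forced random pairing the error rate stayed near nominal.
- A reader might conclude that the ordinal and linear models were swapped and that the CPC analysis is uninterpretable. The article does not list the CPC levels, a linear mixed model on an ordinal score is a common approximation, and a swap is conjecture.

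**Conclusion.** The point holds for secondary outcomes only. The signed-rank test is the wrong test for two independent arms; its direct reach is total cost and any general comparison of a skewed variable, and the harm is a result that depends on arbitrary pairing. The five durations are given a model that contradicts their own description and comes without a rule for death or non-attainment.

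The mismatch itself follows from the text without assumptions. The size of any bias does not: the 3% to 18% range assumes that deaths enter at observed length, uses invented stay distributions and mortality gaps, and replaces the planned model with a rank-sum test. It shows direction and possible scale, and is not a forecast for this trial. The linear model for CPC is a matter of preference, not an error.

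**What to change.** 1. Replace the signed-rank test with the Wilcoxon rank-sum (Mann–Whitney) test.
2. Analyse time to readiness, to ECMO weaning and to ventilator weaning as time-to-event outcomes with death as a competing event, consistent with the Cox and Kaplan–Meier analyses already planned. Drop the ordered logistic model for these three.
3. Analyse ECMO unit and hospital stay either as time to discharge alive with death competing, or as an ordinal outcome such as days alive and out of hospital to day 90 with death ranked worst, by rank-sum or proportional odds without a random effect. State the rule for deaths in the text.
4. Optional: use a mixed-effects ordinal model for repeated CPC. If so, keep a named model for ADL, HRQoL and the diaphragm measures so that none is left without one.

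The cost is analysis wording only. Event dates and deaths are already to be recorded, and neither the sample size nor the visit schedule changes. The change should be made before unblinded data are seen, so that the choice of test cannot depend on the results.

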Upon the above rationale, the upcoming question is that what benefits of cardiopulmonary rehabilitation can be delivered to ECMO-supported patients. For clinicians, ECMO weaning is particularly challenging and annual ECMO mortality has been reported to be approximately ranged 40–70% (10, 11). According to our experience, delayed ECMO weaning also demonstrated worse functional prognosis and impaired health-related quality of life (HRQoL). Previous studies have documented that rate of mechanical ventilation weaning was improved in patients received early rehabilitation intervention, while its effectiveness in ECMO weaning remains unclear (12). Indeed, the successful weaning of ECMO is complex and multifactorial (13). ECMO weaning at the earliest possible time would be expected to improve outcomes, reduce cost, and optimize functional prognosis (14). This inspires us to hypothesize that if the medical rationale is based on its assumed benefits on cardiac function and oxygenation, then cardiopulmonary rehabilitation may subsequently contribute to earlier weaning of ECMO. Our perspective is to provide solutions with the application of cardiopulmonary rehabilitation and convert the aforementioned physiological changes (e.g., increased cardiopulmonary function) into patient-oriented outcomes (e.g., earlier weaning of ECMO and increased rate of ECMO weaning).

Considering the limited evidence in this aspect, ongoing innovation must move from guessing to exploring the effectiveness of cardiopulmonary rehabilitation through an adequately powered trial. Therefore, we design this multidisciplinary randomized controlled trial (RCT) to answer the following clinical question—can cardiopulmonary rehabilitation facilitate weaning of ECMO (CaRe-ECMO)? The results of this trial may subsequently provide innovative treatment solution, specifically the add-on effects of cardiopulmonary rehabilitation to the routine clinical practice for further successful weaning of ECMO.

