### Eligibility and Withdrawal Criteria

The consolidated criteria for patient enrollment are those: (1) aged 18 years or older; (2) eligible for receiving ECMO (VV or VA) therapy; (3) with mechanical ventilation; (4) with stable condition and eligible for cardiopulmonary rehabilitation after 72 h of ECMO; (5) with no contraindications for cardiopulmonary rehabilitation; (6) not pregnant; (7) with a life expectancy of more than 3 days; (8) wean from ECMO therapy within the first 3 days before the initiation of the CaRe-ECMO program; (9) not use ECMO as a bridge to recovery or definitive treatment (e.g., lung transplantation or heart transplantation); (10) not enrolled in another trial previously; and (11) sign informed consent form by the guardian (18). According to previously published guidelines, the specific indications and contraindications for VV-ECMO and VA-ECMO are given in Tables 2, 3, respectively (19, 20).

**Table 2 T2:** Indications and contraindications for VV-ECMO.

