### Data Collection

Data in terms of rate of ready for ECMO weaning, rate of ECMO weaning, rate of mechanical ventilation weaning, all-cause mortality, and rate of major post-ECMO complications will be calculated throughout the index hospitalization and follow-up period (e.g., CaRe-ECMO days 7, 14, 30, and 90) according to daily evaluations recorded in the medical records. Outcomes, for instance ready for ECMO weaning, will be treated as time-to-event outcomes; therefore, date and timing of events will be also recorded to facilitate statistical analysis. Total length of ready for ECMO weaning, total length in hour of ECMO weaning, total length in day of mechanical ventilation, ECMO unit LOS, and total hospital LOS will be collected according to the medical records. CPC index, ADL score, and HRQoL score will be selectively collected among those successfully weaning of ECMO across discharge day (discharge from ECMO unit) and all follow-up time points (e.g., CaRe-ECMO days 30 and 90). In addition, diaphragmatic thickness and mobility will be evaluated with ultrasound (M-mode) every 3 days for determining the allocation of phrenic nerve and the efficacy of SEPNS. The detailed data collection schedule is given in Table 9.

**Table 9 T9:** Scheduled events and timeline of the CaRe-ECMO trial.

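### Readiness and weaning are analysed by Kaplan-Meier and Cox with no rule for death before the event; with deaths censored, the curves overstate the proportions, modestly at day 7 and heavily later

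*Protocol article*

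**What the plan says.** The Data Collection section sets the framework: "Outcomes, for instance ready for ECMO weaning, will be treated as time-to-event outcomes". Statistical Methods then lists the outcomes concerned ("rate of ready for ECMO weaning, rate of ECMO weaning, rate of mechanical ventilation weaning, all-cause mortality, and rate of major post-ECMO complications") and says that group differences in them are to be "estimated with the Cox proportional hazards regression analysis and graphically illustrated using the Kaplan–Meier methods". The stated horizons are days 7, 14, 30 and 90. The sample size is also said to be calculated for a Cox model.

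The Primary Outcome section defines the primary endpoint as a rate of readiness at day 7, that is, a proportion of patients who have met every checklist item.

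Death appears in two relevant places. All-cause mortality is an outcome in its own right in the list above. The Sample Size Calculation also mentions death as a reason to expect little loss to follow-up: "patients treated with ECMO therapy generally will not discharge till stable or death". Nothing in the article says whether a patient who dies before readiness or weaning is censored, kept as a non-event to the horizon, or treated as having a competing event.

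Statistical Methods also has a general rule: "Categorical variables will be compared with the chi-square" or Fisher's exact test, with all outcomes analysed by intention to treat and per protocol. It does not say whether this rule or the Cox model gives the primary comparison.

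**The concern.** A patient who dies on ECMO can no longer become ready or be weaned. Censoring that patient treats the death as uninformative and in effect assumes the patient would have gone on to readiness at the same pace as the survivors. One minus Kaplan-Meier then estimates readiness in a hypothetical setting without deaths, which is not the day-7 rate defined as the primary outcome.

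Deaths before the event must be expected. The Introduction notes that "annual ECMO mortality has been reported to be approximately ranged 40–70" per cent, and eligibility asks only for patients "with a life expectancy of more than 3 days", which does not exclude death before day 7.

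Two things are at stake. The displayed proportions would be too high, increasingly so at later horizons. And the hazard ratio for readiness, read alone, could miss a treatment that lowers the proportion ready by increasing deaths.

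**Working it through.** **Inputs.** From the article: 30% ready by day 7 without and 45% with rehabilitation (Sample Size Calculation); horizons of days 7, 14, 30 and 90. The article gives no death rate by day 7 for this population, so 5% to 30% is an assumed range. The late-horizon figures are also assumed.

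**1. Kaplan-Meier with deaths censored.** Let R be the true proportion ready and D the proportion dead before readiness by the horizon. With constant cause-specific hazards:

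- total cumulative hazard H = −ln(1 − R − D)
- readiness part = H × R/(R + D)
- 1 − KM = 1 − exp(−readiness part)

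| R | D (assumed) | H | readiness part | 1 − KM | excess, points |
|---|---|---|---|---|---|
| 0.30 | 0.05 | 0.431 | 0.369 | 30.9% | 0.9 |
| 0.30 | 0.10 | 0.511 | 0.383 | 31.8% | 1.8 |
| 0.30 | 0.20 | 0.693 | 0.416 | 34.0% | 4.0 |
| 0.30 | 0.30 | 0.916 | 0.458 | 36.8% | 6.8 |
| 0.45 | 0.20 | 1.050 | 0.727 | 51.7% | 6.7 |
| 0.40 (late, assumed) | 0.50 | 2.303 | 1.023 | 64.1% | 24.1 |

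With 20% dead in both arms, the planned 15-point difference (45% against 30%) would be drawn as about 18 points (51.7% against 34.0%).

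**2. Hazard ratio when only the death hazard differs.** Take a readiness hazard of 0.06 per day in both arms and death hazards of 0.03 and 0.10 per day. The proportion ready by day 7 is [r/(r + d)] × [1 − exp(−7(r + d))]:

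- lower-death arm: (0.06/0.09) × (1 − exp(−0.63)) = 31.2% ready, 15.6% dead
- higher-death arm: (0.06/0.16) × (1 − exp(−1.12)) = 25.3% ready, 42.1% dead

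The cause-specific hazard ratio is 1.00, and 1 − KM is 1 − exp(−0.42) = 34.3% in both arms. The loss of about 6 points in readiness is invisible, but the analysis does not favour the arm with more deaths.

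**3. Hazard ratio when deaths fall on patients unlikely to become ready.** This is a simulation with 400,000 patients per arm. Half are low-risk (readiness 0.09, death 0.01 per day) and half high-risk (readiness 0.015, death 0.06 per day). Treatment has no effect on the readiness hazard and triples the death hazard in the high-risk half. Pairs are control, then treated.

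| Horizon | truly ready | dead | 1 − KM | HR, deaths censored | HR, deaths kept as not ready |
|---|---|---|---|---|---|
| Day 7 | 26.7%, 25.4% | 18.9%, 36.9% | 30.0%, 33.6% | 1.13 | 0.95 |
| Day 30 | 51.7%, 46.7% | 40.6%, 50.6% | 74.6%, 88.8% | 1.33 | 0.88 |

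Under these deliberately strong assumptions the direction reverses.

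**4. Would a death-inclusive primary comparison be affordable?** For 30% against 45%, two-sided 5% and 80% power, the patients needed per arm are [1.96 √(2 × 0.375 × 0.625) + 0.8416 √(0.30 × 0.70 + 0.45 × 0.55)]² / 0.15² = 1.911² / 0.0225 = 162.3, so 163 per arm or 326 in total. The plan has 348 before attrition. Power at 174 per arm is 82.7%, or 80.2% with Fisher's exact test.

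**The case against.** The strongest reply is that the article never says deaths are censored. If patients who die stay in the risk set as not ready to the horizon, one minus Kaplan-Meier equals the cumulative incidence and the bias disappears. A censoring rule could also sit in a fuller document that is not shown. This stands in part: the defect is a named method with no rule for death, not a proven wrong estimator. But the article does fix the method, and the ordinary handling under that method does not estimate the endpoint it defines.

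Second, the chi-square or Fisher rule, applied by intention to treat to day-7 readiness, would already count deaths as not ready. That is true, but the rule is not designated as primary, the sample size is tied to Cox, and the curves and the later weaning results would stay uncorrected.

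Third, all-cause mortality is analysed by arm at the same horizons, so a large excess of deaths would be seen beside the readiness result. The article also concedes that open-label rehabilitation for non-responders after day 7 may impair long-term comparison. Both points are fair. They soften the consequence but do not make the curves correct.

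Three stronger readings should be resisted:

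- A reader might take the 40–70% mortality as the death rate acting on the primary endpoint. It is a general annual ECMO figure, not day-7 mortality in patients who were stable after 72 hours. It shows only that deaths will be common.
- A reader might infer that the Cox hazard ratio generally rewards an arm with more deaths. With homogeneous risk it is merely blind to them (step 2). An example that holds the proportion ready equal while one arm has more deaths does not show a reward either: under constant hazards it builds a higher readiness hazard into that arm.
- A reader might conclude that the cause-specific hazard ratio is invalid. It is a legitimate answer to whether readiness comes faster among patients still at risk.

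**Conclusion.** The point holds in limited form. The article assigns Kaplan-Meier and Cox to readiness and both weaning outcomes and gives death before the event no stated role. If deaths are censored, the displayed day-7 readiness is too high by about 1 to 7 points for a true 30% and an assumed 5% to 30% dead, and a late-horizon figure could be too high by about 24 points (64% shown for 40%). These sizes rest on constant hazards and assumed death rates. The cause-specific hazard ratio does not compare day-7 proportions. It can favour the arm with more deaths only if those deaths fall on patients less likely to become ready, and nothing in the article establishes that this will happen.

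**What to change.** - Name as the primary analysis the intention-to-treat proportion of all randomised patients ready by day 7, with death before readiness counted as not ready, reported as a risk difference with 95% CI.
- Replace the Kaplan-Meier curves for readiness, ECMO weaning and ventilator weaning by Aalen-Johansen cumulative incidence curves with death as a competing event. Keep Kaplan-Meier for all-cause mortality.
- Report the cause-specific hazard ratio for readiness together with the one for death. A subdistribution hazard ratio is optional; ranking it above the cause-specific one is a choice of estimand, not a correction.
- Settle this before any unblinded outcome data are seen, because the handling of death can change the result.

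The cost is analysis wording and slightly lower displayed readiness. Dates of death are already needed for the mortality outcome. No extra patients are required (326 against the planned 348), provided that the planning values of 30% and 45% are crude proportions with deaths in the denominator. The article does not say so, and the revised text should.

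### The subgroup analysis aims at heterogeneity of the treatment effect, but the method named for it does not, as written, test whether the effect differs between subgroups

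*Protocol article*

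**What the plan says.** One sentence in the Statistical Methods section of the protocol article covers subgroups. Its aim is clear: "we will assess the heterogeneity of the treatment effect on primary outcome and secondary outcomes in pre-specified subgroups of interest". The factors are baseline variables given as examples: "e.g., age, gender, main diagnosis, comorbidities, the APACHE II score, ECMO mode, length since mechanical ventilation". The means are described as exploratory, post hoc "sensitivity adjusted analyses for any corresponding statistical methods mentioned above".

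The methods above that sentence are between-arm comparisons. For simple comparisons: "Categorical variables will be compared with the chi-square or Fisher's exact tests and continuous variables will be compared with the Student's" t-test or the Wilcoxon test. For the time-to-event outcomes, which include readiness for weaning, differences "between the groups will be estimated with the Cox proportional hazards regression analysis". Mixed-effects ordered logistic and mixed-effects linear models cover the rest. The article names no interaction term and no other test of a difference between subgroups. The section closes by putting every analysis at one level: "All the analyses will be conducted at a two-sided alpha level of 5" per cent.

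**The concern.** Heterogeneity has its own null hypothesis: that the treatment effect is equal across levels of the factor. The named method can be read in two ways, and neither addresses that null.

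- **Pooled model adjusted for the factor.** The treatment term tests whether the effect is zero, given the factor.
- **Separate runs by subgroup.** Each run tests whether the effect is zero in that subgroup. Comparing which p-values fall below 5% is not a test of a difference.

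The wording has two further faults. The subgroups are called pre-specified while their analysis is called post hoc. The reason offered, that some patients will not reach the endpoint, does not explain why effect heterogeneity is examined.

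The question matters most for ECMO mode. VV and VA patients are declared ready by different checklists (Tables 5 and 6), and the Discussion hopes for a programme that helps every type of ECMO patient. Readers will look at the effect by mode.

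**Working it through.** The plan gives no figure for the subgroup analysis, so the check is what each candidate analysis detects at the planned size.

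**Inputs.** From Sample Size Calculation: 348 patients before attrition, 1:1, readiness at day 7 rising from 30% to 45%. From Statistical Methods: two-sided 5% and Cox regression for readiness. Assumed: one binary factor split 50/50, with uneven splits as the range. The 348 is taken as stated. That section also gives "effect size of HR = 0.5", which with 30% events leads to 66 / 0.30 = 220 patients (Schoenfeld), not 348. That is a separate matter, so the rates are used here.

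1. **Effect and events.** HR for becoming ready = ln(0.55) / ln(0.70) = 1.68, log 0.516. Expected events = 348 × (0.30 + 0.45) / 2 = 130.5.

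2. **Pooled treatment term, uniform effect.** SE = √(4 / 130.5) = 0.175. Power = Φ(0.516 / 0.175 − 1.96) = 84%. A Cox simulation (4,000 runs, censored at day 7) gave 83% for the adjusted treatment term and 4.9% for the interaction term. The 83% is ordinary main-effect power. It carries no information about heterogeneity, which is absent here.

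3. **Separate subgroups, uniform effect.** Events per subgroup = 65.25, SE = √(4 / 65.25) = 0.248, power in each = Φ(0.516 / 0.248 − 1.96) = 55%. Chance that exactly one is significant = 2 × 0.55 × 0.45 = 50%; the simulation gave 48%. With a 30/70 split, events are 39.15 and 91.35, powers 37% and 69%, and the chance is 0.37 × 0.31 + 0.69 × 0.63 = 55%. With a 20/80 split, powers are 26% and 75%, and the chance is 0.26 × 0.25 + 0.75 × 0.74 = 62%.

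4. **Opposite effects (HR 1.68 and 0.60), an illustration only.** The simulation gave 8% rejection for the pooled adjusted term and 73% for the interaction term.

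5. **Power of the interaction test.** With a 50/50 split and 130.5 events, SE of the log ratio of hazard ratios = √(16 / 130.5) = 0.350. Power = Φ(ln(ratio) / 0.350 − 1.96): 21% for a ratio of 1.5, 31% for 1.68 and 51% for 2.0. With a 30/70 split, SE = √(4 / 39.15 + 4 / 91.35) = 0.382, giving 18% for 1.5 and 44% for 2.0.

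**The case against.** The strongest reply is that the article does not fix a wrong test. It does not say what is adjusted for, whether models are pooled or run by subgroup, or which term is examined. Chi-square, Fisher, t and Wilcoxon tests take no covariates, so the word adjusted points to the Cox and mixed models, which accept an interaction term. The exact model could sit in an analysis plan that is not shown. The analyses are exploratory, no rule for claiming a subgroup difference is given, and neither the primary test nor the sample size depends on them.

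Much of this stands. An interaction term is not excluded, and the primary conclusion is untouched. But the article is not simply silent: it names the means by which heterogeneity will be assessed, and what it names does not match the aim. An analysis plan that followed the sentence literally would inherit the mismatch.

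A reader might also infer that the plan will both report false splits between subgroups and miss a benefit in one ECMO mode with harm in the other. These two harms come from different readings. The first needs separate subgroup runs; the second needs a pooled model with no subgroup estimates, which sits badly with a plan to look within subgroups. They should not both be charged to one analysis. The documents also give no VV/VA split and no reason to expect harm in either mode.

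**Conclusion.** The point holds as a mismatch between aim and method in an exploratory analysis. On either reading, the analysis described does not test whether the effect differs between subgroups. If subgroups are run separately and their p-values compared, a uniform 30% to 45% effect would produce a misleading split for one binary factor in about half of trials with a 50/50 division, and somewhat more often with an uneven one. This rests on the stated 348 patients and rates, on proportional hazards to day 7, and on the assumed splits.

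The stronger inference, that the trial will reject or fail to reject for the wrong reason, is not supported: no decision rule is attached to these analyses. Nor should the figure be scaled up to all seven example factors as if they were independent halves, since age and APACHE II are continuous, and main diagnosis and comorbidities are not single binary factors.

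**What to change.** - For the primary outcome, and for secondary outcomes where subgroups are examined, add treatment-by-subgroup interaction terms to the corresponding regression model (Cox for readiness). Use a joint test for multi-level factors such as main diagnosis.
- Report each subgroup effect with its 95% confidence interval, together with the interaction p-value. State that within-subgroup p-values will not be used to claim a difference.
- Call the analysis pre-specified exploratory and delete the post hoc label.
- List covariate-adjusted main-effect models separately, as sensitivity analyses of the overall effect.

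The cost is a change of wording and some extra model terms (more than one for multi-level factors), using baseline data already collected. The downside should be stated in the plan: interaction power is low, roughly 21% to 51% for ratios of hazard ratios of 1.5 to 2.0 with a 50/50 split, so few subgroup claims will be supported and a non-significant interaction will not show that effects are equal. Seven interaction tests at 5%, if independent, would still give at least one false positive in 1 − 0.95^7 = 30% of trials, which is a further reason to keep the exploratory label.
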